4.[2](#_bookmark25) It is expressed on the cell surface of activated T-cells under normal conditions[.^2^](#_bookmark25) By binding to its ligand (PD-L1 and PD-L2), PD-1 down-regulates T-cell activation and therefore dampens unwarranted and excessive immune responses, including autoimmunity. Melanoma cells exploit the PD-1 checkpoint pathway to evade immune surveillance. The interaction between PD-L1 expressed on tumor and stromal cells and PD-1 on T cells can trigger inhibitory signaling pathways that reduce effector cell functions and T-cell-killing capacity. Blocking the PD-1/PD-L1 interaction has been shown to potentiate tumor-specific CD8+ T-cell infiltration and effector T-cell activation that promote tumor rejection[.^9^](#_bookmark30)[^,10^](#_bookmark31)

- 1. Pembrolizumab for advanced melanoma

Pembrolizumab is a human IgG4 PD-1 blocking antibody that is recently approved by the FDA for the treatment of patients with unresectable or metastatic melanoma and disease, including progression following ipilimumab and, if BRAF V600 mutation positive, a BRAF inhibitor. Pembrolizumab showed an unprecedented rate of durable clinical responses, with an overall response rate of 26% and median progression-free survival of 22 weeks (95% CI: 12-36 weeks)[.^8^](#_bookmark29) Treatment has generally been well-tolerated, and the most common drug-related adverse events (AEs) of any grade were fatigue (33%), pruritus (26%), and rash (18%). Patients responding to treatment showed proliferation of CD8 T cells in their tumors.[^10^](#_bookmark31)

Despite the promising data associated with pembrolizumab treatment, the majority of melanoma patients treated does not respond to pembrolizumab. Several possible mechanisms for pembrolizumab (and other PD-1 blockade) resistance exist, including additional mechanisms of immunosuppression in the tumor microenvironment and derangements in systemic immune competence[.^11^](#_bookmark32)[^,12^](#_bookmark33) Specifically, it has been demonstrated that patients with metastatic melanoma have increased regulatory T-cells and Th2 cells[.^13^](#_bookmark34)[^,14^](#_bookmark35) Our previous study has shown that patients with advanced melanoma have elevated Th2 cytokines that incapacitate anti-tumor immune responses[.^15^](#_bookmark36) Such a dysregulation can serve as a barrier for successful immunotherapy.

- 1. Ibrutinib

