Recent studies revealed that in addition to BTK, ibrutinib can also specifically inhibit IL-2-inducible kinase (ITK). Ibrutinib irreversibly binds to ITK and inhibits Th2 cell differentiation and activation[.^27^](#_bookmark46)[^,28^](#_bookmark47) Given the redundant role of resting lymphocyte kinase (RLK) to ITK in Th1 and CD8 T-cells, inhibition of ITK provides a platform for preferential activation of Th1 and CD8 T-cells, and therefore skews immune polarity in favor of Th1-based immune responses. Th1/Th2 skewing as well as increased CD8 T cell responses was confirmed in mouse models treated with ibrutinib.[^27^](#_bookmark46) Ibrutinib treatment in murine models also showed ameliorated chronic graft-versus-host disease, a condition mediated by B cell, and specific CD4+ T cell subset, due to BTK and ITK inhibition^28^.

The immunomodulatory effects of ibrutinib suggest that it can potentially be used to enhance antitumor immune response in combination with other immunotherapy modality. In a recent study performed in a mouse model with ibrutinib insensitive lymphoma, the combination of anti–PD-L1 antibody and ibrutinib suppressed tumor growth^29^.

- 1. Rationale for the proposed study

Based on the observations that 1) melanoma patients frequently exhibit evidence of Th2 polarization of immune responses, 2)Th2 polarization can compromise the ability of the immune system to eradicate melanoma cells, and 3) ibrutinib skews T cell responses toward an anti-tumor Th1 phenotype; we propose to test whether the combination of ibrutinib and pembrolizumab immunotherapy leads to an improvement in the objective response rate of advanced melanoma patients over that expected by pembrolizumab alone. In so doing, we will determine whether ibrutinib therapy drives a change in Th1/Th2 immune polarity favoring Th1 anti-tumor immune responses.

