3.29l Unresolved toxicities from prior anti-cancer therapy, defined as not resolved to Common Terminology Criteria for Adverse Events (CTCAE, v4.0) Grade 0 or 1, or to the levels dictated in the inclusion/exclusion criteria with the exceptions of alopecia and peripheral neuropathy.

- 1. Registration – Inclusion Criteria
  2. Histologic or cytologic confirmation of unresectable stage III or metastatic melanoma (stage IV) not amenable to local therapy.
  3. Only if patient has had previous exposure to anti-PD-1 or anti-PD-L1 therapy:
     1. Patient had disease progression on or within 6 months after anti-PD-1/anti-PD- L1 therapy in the metastatic setting

**OR**

- - 1. Patient had disease progression within 6 months after the last dose of adjuvant/neoadjuvant anti-PD-1/anti-PD-L1 treatment
  1. The following laboratory values obtained ≤14 days prior to registration.
- Absolute neutrophil count (ANC) ≥1000/mm^3^
- Platelet count ≥75,000/mm^3^*
- Hemoglobin ≥9.0 g/dL
- Total bilirubin ≤1.5 X upper limit of normal (ULN); if total bilirubin >1.5 X ULN then direct bilirubin ≤ ULN
- Aspartate transaminase (AST) and alanine transaminase (ALT) ≤2.5 x ULN

**OR** ≤5 X ULN for patients with liver metastases

- Creatinine ≤1.5 X ULN and CrCL ≥30 ml/min per Cockcroft Gault formula

[figure not shown]

*Criteria must be met without a transfusion ≤four weeks prior to registration.

- 1. Patients of childbearing potential only: negative urine pregnancy test done

≤7 days prior to study registration.

- 1. Registration – Exclusion Criteria
  2. Failure to confirm histologically or cytologically unresectable stage III or metastatic melanoma (stage IV) not amenable to local therapy.
  3. Prior chemotherapy, immunotherapy, radioactive, or biological cancer therapy (including mAb) ≤28 days prior to registration.
  4. Received a strong cytochrome P450 (CYP) 3A inhibitor ≤7 days prior to registration
  5. Concurrent systemic immunosuppressant therapy ≤21 days prior to registration.
  6. Recent infection requiring systemic antibiotic treatment that was completed ≤14

days prior to registration.

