# Statistical Considerations and Methodology

- 1. Background

A 3+3 phase I clinical trial design will be used to determine the maximum tolerated dose of Ibrutinib when used in combination with Pembrolizumab in patients with metastatic melanoma who are Ipilimumab-naïve in the metastatic setting. Once determined, a dose expansion cohort will be used to determine an early signal of promising anti-tumor activity measured by tumor response.

- 1. Study Design – Phase I
  2. Definition of Maximum Tolerated Dose (MTD)

The maximum tolerated dose is defined as the highest dose level among those tested where at most one out of 6 patients develops a DLT prior to the start of their second cycle of treatment and the next highest dose level is such that 2 out of a maximum of 6 patients treated at this dose level developed a DLT prior to the start of their second cycle of treatment.

- 1. Enrollment and determination of MTD

16.221 A minimum of 2 or a maximum of 6 patients will be accrued to a given dose level.

For each dose level, patients will be accrued so that at any given time no more than 2 patients will be receiving their first cycle of treatment **and** acute adverse event data over the first treatment cycle for all other patients treated at the current dose level is known.

16.222 If, at any time in the enrollment process, 2 patients treated at the current dose level develop a DLT during the first cycle of treatment, enrollment will be closed to that dose level. Enrollment will be re-opened to the next lower dose level if fewer than 6 patients have been treated at that dose level in order to establish whether it is the MTD.

If none of the first 3 patients treated at a given dose level develops a DLT during the first cycle of treatment, enrollment to the dose level will be closed and enrollment will reopen at next higher dose level. If there are no other higher dose levels to be tested, three additional patients will enrolled at the current dose level to confirm MTD.

If one of the first 3 patients treated at a given dose level develops a DLT during the first cycle of treatment, three additional patients will enrolled (sequentially) onto the current dose level.

- If, at any time in the enrollment of these 3 additional patients, a patient develops a DLT, enrollment will be closed to this dose level. Enrollment will be re-opened to the next lower dose level if fewer than 6 patients have been treated at that dose level.

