- If none of these 3 additional patients develops a DLT during the first cycle of treatment, enrollment to this dose level will be closed and enrollment will reopen at next higher dose level. If there are no other higher dose levels to be tested, this will be considered the MTD
  1. Study Design – Expansion Cohort (Treated at MTD)

Acknowledging both the short term aspect of the primary endpoint of the study and that 18 patients may be enrolled, we have chosen a phase II study design proposed by Gehan30. Two (2) responses in 14 eligible patients having initiate treatment will be considered indicative of promising activity and further study in a phase 2 study. According to Gehan, if a drug were 20 percent effective or more, there would be a 95% chance that one or more successes would be obtained in 14 patients^30^.

Gehan’s approach calculated cumulative probability of observing at most x successes in N patients (i.e., assuming a binomial distribution) assuming the true success rate is P.

Assuming true success (response) proportion in 14 patients is P=20%:

| If the number of responses (x) observed… | Then the probability of observing  ≤ x responses is less than or equal  to… |
| --- | --- |
| 0 | 0.044 |
| 1 | 0.198 |
| 2 | 0.448 |
| 3 | 0.698 |

Assuming true success (response) proportion in 14 patients is P=30%:

| If the number of responses observed… | Then the probability of observing  ≤ x responses is less than or equal  to… |
| --- | --- |
| 0 | 0.007 |
| 1 | 0.047 |
| 2 | 0.161 |
| 3 | 0.355 |

Two planned safety checks will occur after 3 and 6 patients have completed their first cycle of treatment. If we observe DLT(s) at either review of the data (1 DLT in the first 3 patients or 2 DLTs in the first 6 patients), we will drop the starting dose level to 280 mg and continue with the remainder of the study. Only one reduction in the starting dose level will be allowed. All data will be summarized by assigned starting dose level and by prior ICI therapy status.

- 1. Sample Size

Enrollment and anticipated number of patients, phase of study:

- - - Prior to MCCC Amendment #2, two patients were enrolled and the study was stopped due to toxicity. The study reopened was modified to a phase I (vs phase II).
    - Phase I - During the dose escalation phase, a minimum of 9 and a maximum of 18 patients is anticipated. Enrollment was completed prior to MCCC Amendment #6 (11 patients).

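### The 2-of-14 criterion (14.3%) lies below the 26% response rate quoted for pembrolizumab alone, so meeting it shows activity of the regimen and not a gain from ibrutinib

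*Protocol*

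**What the plan says.** - **Rule (Section 16.3).** "Two (2) responses in 14 eligible patients having initiate treatment will be considered indicative of promising activity", and on that basis worth taking into phase 2. I read this as two or more responses.
- **Justification of n = 14 (Section 16.3).** A Gehan screen: "if a drug were 20 percent effective or more, there would be a 95% chance that one or more successes would be obtained in 14" patients. Cumulative probabilities are tabulated for true rates of 20% and 30% only.
- **Background rate (Section 1, pembrolizumab for advanced melanoma).** Pembrolizumab is described "with an overall response rate of 26% and median progression-free survival of 22 weeks".
- **Question (Section 1, rationale).** Whether the combination "leads to an improvement in the objective response rate of advanced melanoma patients over that expected by pembrolizumab alone".
- **Treatment (Section 7).** Every patient receives pembrolizumab together with ibrutinib.
- **Population.** Section 3 applies a progression requirement "Only if patient has had previous exposure to anti-PD-1 or anti-PD-L1 therapy". Naive and previously treated patients are therefore both eligible, and no proportion is set. Section 16.1 instead describes a trial "in patients with metastatic melanoma who are Ipilimumab-naïve in the metastatic setting", which no criterion in Section 3 selects.
- **Reporting.** Section 16.3 summarises all data by prior ICI status, but the 2-of-14 count is pooled. Section 16.6 reports response with binomial confidence intervals and treats all results as exploratory.

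**The concern.** A Gehan screen asks whether a treatment has any activity, against a background of little or none. Here the regimen contains a drug that the protocol itself treats as active. The bar lies below the response rate quoted for that drug, and neither a pembrolizumab-based null rate nor a false-go probability is attached to it.

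At stake is how a positive result is read. In anti-PD-1-naive patients, two responses are what pembrolizumab alone would usually produce. The rule could then send the combination to phase 2 with a label of promise although ibrutinib added nothing, or although the regimen did worse than the quoted 26%. Pooling makes this harder to see, because two responses among refractory patients mean something different from two among naive patients.

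**Working it through.** **Inputs.** n = 14, the threshold of 2 responses, and the exact binomial model are from Section 16.3 ("assuming a binomial distribution"). The 26% is from Section 1. The rates for refractory patients are my assumption; the protocol gives none.

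**Step 1: reproduce the plan's figures.** With X ~ Binomial(14, p), P(X = 0) = (1 − p)^14 and P(X ≤ 1) = (1 − p)^14 + 14p(1 − p)^13.

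- p = 0.20: P(X = 0) = 0.0440, so P(X ≥ 1) = 0.956, the stated 95%. P(X ≤ 1) = 0.0440 + 0.1539 = 0.1979; the table has 0.198.
- p = 0.30: P(X = 0) = 0.0068 and P(X ≤ 1) = 0.0475; the table has 0.007 and 0.047.

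The entries for 2 and 3 responses also agree (0.4481 and 0.6982 at 20%; 0.1608 and 0.3552 at 30%). The tables are correct.

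**Step 2: compare the bar with the background rate.** 2/14 = 14.3%, against 26%. An observed 2/14 has an exact 95% interval of 1.8% to 42.8%. At the threshold the data are compatible with pembrolizumab alone and with much lower rates.

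**Step 3: chance of meeting the rule when ibrutinib adds nothing and all 14 patients share one true rate.** P(X ≥ 2) = 1 − P(X ≤ 1).

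| True rate | P(at least 2 of 14) |
| --- | --- |
| 12% | 0.514 |
| 20% | 1 − 0.198 = 0.802 |
| 26% | 1 − (0.0148 + 0.0727) = 0.913 |
| 30% | 1 − 0.0475 = 0.953 |

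The true rate without ibrutinib would have to be just under 12% before this chance fell below one half.

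**Step 4: mixed cohort.** Let k patients be naive with p = 0.26 and 14 − k refractory with rate q.

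- P(0) = 0.74^k (1 − q)^(14−k)
- P(1) = 0.26k · 0.74^(k−1) (1 − q)^(14−k) + (14 − k)q(1 − q)^(13−k) · 0.74^k
- The rule is met with probability 1 − P(0) − P(1).

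For k = 7 and q = 0.05: P(0) = 0.0849, P(1) = 0.2400, and the result is 0.675.

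| Naive patients of 14 | q = 5% (assumed) | q = 10% (assumed) |
| --- | --- | --- |
| 14 | 0.913 | 0.913 |
| 10 | 0.811 | 0.840 |
| 7 | 0.675 | 0.754 |
| 0 | 0.153 | 0.415 |

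**The case against.** The best defence is that the rule was never a comparison. Section 2 gives the expansion cohort an estimation goal, Section 16.1 speaks of an early signal of activity, and the wording about improvement sits in the background rationale. Section 16.6 adds confidence intervals, calls every finding hypothesis-generating and notes the heterogeneous population. The tables in Section 16.3 already imply pass probabilities of 80% and 95%, which bracket the 91%.

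Most of this stands, and it lowers the severity. It does not remove the problem. Section 16.3 still fixes a trigger for phase 2, the rationale still names pembrolizumab alone as the comparison, and nowhere does the protocol say that the trigger cannot speak to that comparison.

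The benchmark is also open to challenge. The study cited for the 26% is titled as one in ipilimumab-refractory melanoma, whereas Section 16.1 speaks of ipilimumab-naive patients. This trial counts a response only if it is met on two evaluations at least 8 weeks apart, and nothing shows that the 26% used that definition. So 26% is approximate. It is, however, the only pembrolizumab response rate the protocol offers, and the conclusion is the same anywhere from 20% to 30%.

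Three stronger readings are tempting, and the document does not support them:

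- *The trial has a 91% false-go rate.* That needs 14 naive patients responding at 26%. The case mix is not fixed, and Step 4 shows how far the figure can fall.
- *Meeting the rule says nothing about ibrutinib.* In patients who progressed on anti-PD-1/PD-L1 therapy, responses are more informative.
- *The threshold must be replaced.* Against 26%, 6 of 14 would give a false go of 0.130 and 7 of 14 would give 0.047, but the protocol names no target rate from which to choose. Counting two responses among refractory patients only has its own price: with 7 such patients and a true 20%, P(at least 2) = 1 − 0.8^7 − 7(0.2)(0.8^6) = 0.42, against 0.80 with 14. Six of the 14 were already enrolled at Amendment 6, so a new bar now could be data-dependent.

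**Conclusion.** The point holds as a matter of what the criterion can show. A bar of 14.3% lies below the protocol's own 26% for a drug that every patient receives, and the false-go risk at that rate is not stated. In an all-naive cohort at 26% with no ibrutinib effect the rule is met with probability 0.913 (0.80 to 0.95 for background rates of 20% to 30%). With half the cohort naive it is about 0.68–0.75, and with none about 0.15–0.42, both resting on assumed refractory rates of 5–10%. Meeting 2/14 supports activity of the regimen; in anti-PD-1-naive patients it cannot by itself support a contribution from ibrutinib.

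Severity is moderate. The cohort is exploratory, the goal is estimation, and the only consequence is further study.

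**What to change.** In Section 16.3, with n unchanged:

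1. Add a 26% column to the probability tables, and state that two or more responses in 14 occur with probability of about 0.91 at that rate. Label this as the chance of a false go if all patients are anti-PD-1-naive and ibrutinib adds nothing, and call 26% an approximate benchmark.
2. State that meeting 2/14 indicates activity of the regimen, not improvement over pembrolizumab, and cannot by itself support an ibrutinib contribution in anti-PD-1-naive patients.
3. Report the response rate with an exact confidence interval separately by prior anti-PD-1/PD-L1 status. Read the naive estimate against 26%, and base any statement on added ibrutinib activity on these strata and not on the pooled count. The planned summary by prior ICI status comes close to this, but its label should be defined so that the split is on anti-PD-1/PD-L1 exposure.

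Reconcile the ipilimumab-naive population in Section 16.1 with the eligibility criteria in Section 3.

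The cost is wording only. The stated operating characteristic becomes less favourable, and the strata will be small with wide intervals. A new numerical bar or a refractory-only count is optional; either would need its own operating characteristics and a statement of what data had been seen when it was set.
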